# Study protocol: the Fueling Learning through Exercise (FLEX) study – a randomized controlled trial of the impact of school-based physical activity programs on children’s physical activity, cognitive function, and academic achievement

**DOI:** 10.1186/s12889-016-3719-0

**Published:** 2016-10-13

**Keywords:** School children, School-based physical activity intervention, Executive function, Childhood obesity, Health disparities

## Abstract

**Background:**

Physical activity (PA) is critical to preventing childhood obesity and contributes to children’s overall physical and cognitive health, yet fewer than half of all children achieve the recommended 60 min per day of moderate-to-vigorous physical activity (MVPA). Schools are an ideal setting to meeting PA guidelines, but competing demands and limited resources have impacted PA opportunities. The Fueling Learning through Exercise (FLEX) Study is a randomized controlled trial that will evaluate the impact of two innovative school-based PA programs on children’s MVPA, cognitive function, and academic outcomes.

**Methods:**

Twenty-four public elementary schools from low-income, ethnically diverse communities around Massachusetts were recruited and randomized to receive either *100 Mile Club®* (walking/running program) or *Just Move™* (classroom-based PA program) intervention, or control. Schoolchildren (grades 3–4, approximately 50 per school) were recruited to participate in evaluation. Primary outcome measures include PA via 7-day accelerometry (Actigraph GT3X+ and wGT3X-BT), cognitive assessments, and academic achievement via state standardized test scores. Additional measures include height and weight, surveys assessing psycho-social factors related to PA, and dietary intake. School-level surveys assess PA infrastructure and resources and intervention implementation. Data are collected at baseline, mid-point (5–6 months post-baseline), and post-intervention (approximately 1.5 years post-baseline). Demographic data were collected by parents/caregivers at baseline. Mixed-effect models will test the short- and long-term effects of both programs on minutes spent in MVPA, as well as secondary outcomes including cognitive and academic outcomes.

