## Methods/Design

### Aims

The primary aim of the FLEX Study is to evaluate the impact of two school-based PA programs, *100 Mile Club®* and *Just Move™*, on children’s school-time MVPA and total daily MVPA, compared to a control group. In addition, the RCT will evaluate the effects of these innovative, school-based PA programs on children’s cognitive performance and academic achievement. The study will also evaluate the reach of the programs by examining factors that influence participation among different demographic, weight status, and fitness groups.

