## Data collection methods

### Overview

Detailed information about study measures and time points is presented in Table 1.

**Table 1 Tab1:** Data collection plan for the FLEX Study

	Baseline (School Year 1)	Midpoint (School Year 1)	Post-Intervention (School Year 2)	Once per school year
Participant level measures				
Primary outcome measures				
Physical activity (accelerometry)	√	√	√	
Cognitive function (Digit Span and Stroop Color-Word tests)	√	√	√	
Standardized test scores	√^a^	√	√	
Attendance	√^a^	√	√	
Anthropometric measures				
Height	√	√	√	
Weight	√	√	√	
Additional physical activity measures				
Social support for PA	√	√	√	
What Kind of Kid Are You? (self-perception of behavior, athletic competence and global self-worth)	√	√	√	
Cardiorespiratory fitness (PACER)				√
Dietary measures				
Weekday breakfast consumption	√	√	√	
7-day dietary recall	√	√	√	
Demographic measures				
Date of birth	√			
Grade	√			
Sex	√			
Race/Ethnicity	√			
Free/reduced price lunch eligibility	√			
Behavioral/developmental difficulties	√			
Individualized education program status	√			
Maternal education level	√			
Paternal education level	√			
School-level measures				
School physical activity environment scan				√
School food environment scan				√
Program evaluation measures (100 Mile Club and Just Move schools)				
Participant-level program participation and attitudes		√	√	
Champion/teacher program questionnaire	√	√	√	
Direct observation				√

^a^Collected in the spring of the prior year

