### Academic outcomes

Individual child-level standardized test scores will be collected from the Massachusetts DESE and used as an indicator of academic achievement. PA in children has been shown to be positively associated with scores on both Math and ELA [33, 34]. The Massachusetts Comprehensive Assessment System (MCAS) test has been used in Massachusetts annually for all students in grades 3–10. During the 2014–2015 academic year, the DESE began the process of transitioning to a different standardized test, the Partnership for Assessment of Readiness for College or Careers (PARCC). The MCAS/PARCC tests are administered annually in the spring and coincide with both mid- and post-intervention measurements. Baseline standardized test scores (year prior to enrollment) will be obtained retrospectively and for each year of participation for all participants. For both tests, raw scores are converted to scaled scores, which are linked to four levels that describe the performance levels of individual students, schools, and districts: Advanced, Proficient, Needs Improvement, and Warning. Additionally, grade-level standardized test scores will be collected across grades 3–5, and will be aggregated to analyze school-level impact of *100 Mile Club* and *Just Move*.

School attendance will be collected and examined as an exploratory outcome at the individual and school level. Attendance will be assessed as the number of days present per academic school year and converted to a percentage.

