For statistical analyses, descriptive statistics for variables of interest will be compiled and tabulated. To test the effect of school-based PA programs on minutes spent in MVPA, we will compare *100 Mile Club* vs. control and *Just Move* vs. control as separate tests using mixed effects models. Outcomes of interest are changes in minutes of MVPA between midpoint vs. baseline and post-intervention vs. baseline. The key regression coefficient of interest is the intervention by time interaction term, which will indicate if the intervention is associated with a significant higher/lower change in MVPA across time compared to the control. The unique school identification number will be modeled as random intercepts to adjust for clustering. We will examine both unadjusted and adjusted (including covariates such as sex, race/ethnicity, weight status) regression coefficients of the respective program and conclude if the difference in MVPA minutes is statistically significant. A similar approach will be used to examine the impact of PA programming on academic/cognitive outcomes. All analyses will be performed using SAS 9.3 (Cary, NC, USA) and results with p-values less than 0.05 will be considered statistically significant.

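### Cognitive and academic outcomes are labelled both primary and secondary, attendance both primary and exploratory, and no MVPA test is named as deciding although every analysis is judged at p<0.05

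*Protocol article*

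**What the plan says.** **Cognition and academic achievement.**
- The abstract's Methods paragraph states "Primary outcome measures include PA via 7-day accelerometry (Actigraph GT3X+ and wGT3X-BT), cognitive assessments, and academic achievement via state standardized test scores". Its last sentence describes tests on minutes of MVPA "as well as secondary outcomes including cognitive and academic outcomes".
- Table 1 puts accelerometry, the cognitive tests, standardized test scores and attendance under the heading "Primary outcome measures".
- The body section headed Primary outcomes has subsections for physical activity, cognitive performance and academic outcomes.
- The Aims section gives the primary aim as the effect on "school-time MVPA and total daily MVPA, compared to a control group". Cognition and achievement follow in a separate sentence: "In addition, the RCT will evaluate the effects of these innovative, school-based PA programs".

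**Attendance.** It is a primary measure in Table 1. In Academic outcomes, which sits within the Primary outcomes section, the text reads "School attendance will be collected and examined as an exploratory outcome at the individual and school level".

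**Analysis rule** (Sample size calculation and data analyses). Each programme is compared with control in its own test. Two changes are of interest: midpoint against baseline and post-intervention against baseline. The key coefficient is the intervention-by-time interaction. On models the text says "We will examine both unadjusted and adjusted" coefficients and then draws the conclusion on significance from them. Academic and cognitive outcomes get a similar approach. For all analyses, "results with p-values less than 0.05 will be considered statistically significant".

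**Sample size** (same section). Only MVPA is sized: 115 per arm for school-time MVPA, 39 per arm for total daily MVPA, and 903 students after clustering and attrition.

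**The concern.** One paragraph gives the same outcomes two ranks, and the rest of the article divides along the same line: Table 1 and the section heading on one side, the Aims and the sample size on the other. An analysis plan cannot settle this unless the protocol text is also corrected, because a reader of the published protocol could cite either rank.

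The ranking fixes the size of the primary family. Under one reading the primary claim concerns MVPA; under the other, a result on Stroop, digit span, Math or ELA counts as a primary result too. Even with the MVPA reading, several p-values bear on the same claim and each is called significant below 0.05. If school-time and total daily MVPA disagree, or midpoint and post-intervention, or the unadjusted and adjusted models, the text does not say which carries the conclusion. The choice could then be made after the results are seen.

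**Working it through.** **1. The plan's own sample size.** Inputs from the sample size section: 53.4 ± 25.6 against 43.5 ± 27.6; 80% power; 7 schools per arm; ICC 0.03; attrition 25% per year. A two-sided alpha of 0.05 is assumed, since sidedness is not stated.
- Difference 53.4 − 43.5 = 9.9; pooled SD = √[(25.6² + 27.6²)/2] = 26.62.
- n = 2 × 26.62² × (1.960 + 0.842)² / 9.9² ≈ 114 per arm; the t-based version gives 114.5, so 115.
- Total MVPA (difference 26, SD 40): 38 per arm, or 39 with the t-based version.
- Fixed number of clusters: m = n(1 − ICC)/(k − n × ICC) = 115 × 0.97/(7 − 3.45) = 31.4, so 32 per school. Then 32/0.75 = 42.7, so 43, and 43 × 21 = 903.

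All three figures reproduce at an unadjusted 0.05 with MVPA only. No cognitive or academic outcome and no multiplicity allowance enters the design.

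**2. Counting the tests.** This tally is made from the measures the article lists.
- MVPA: 2 measures (Aims) × 2 programmes × 2 time contrasts = 8; for one programme, 4.
- Adding digit span forward, digit span backward, Stroop, Math and ELA: 7 × 2 × 2 = 28.
- Adding attendance: 8 × 2 × 2 = 32.

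**3. Chance of at least one false positive, each test at 0.05.** Under independence it is 1 − 0.95^k. The last column simulates correlated normal test statistics (200,000 draws) under assumed correlations: 0.5 between the two programme contrasts (shared control), 0.5 between the time contrasts, and 0 to 0.7 between outcomes. The documents give none of these correlations.

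| Primary family | Tests | If independent | Assumed correlations |
|---|---|---|---|
| MVPA, one programme | 4 | 18.5% | not run |
| MVPA, both programmes | 8 | 33.7% | 26–30% |
| plus cognition and academics | 28 | 76.2% | 48–71% |
| plus attendance | 32 | 80.6% | 51–76% |

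**4. Unadjusted and adjusted versions.** These are near-duplicates of the same contrast. With an assumed correlation of 0.95 between versions, the 8-test error rises from about 25% to 31% (common correlation 0.5 among the 8) or from about 19% to 24% (common correlation 0.7). Sixteen independent tests would give 1 − 0.95^16 = 56%.

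**5. Power if the primary alpha is split in two.** Effective n per arm = k·m/[1 + (m − 1) × 0.03].
- Planned: m = 43 × 0.75 = 32.25, k = 7; 225.75/1.9375 = 116.5. Power is 81% at 0.05 and 72% at 0.025.
- Enrolled: 174 + 1008 = 1182 children in 24 schools, 49.25 per school; × 0.75 = 36.9; k = 8 assumed; 295.5/2.078 = 142.2. Power is 81% at 0.025.
- Enrolled, with 25% lost in each of two years: m = 49.25 × 0.5625 = 27.7; 221.6/1.801 = 123.1. Power is 75% at 0.025.

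**The case against.** MVPA is primary wherever the article ranks outcomes, it is the only outcome sized, and it leads the analysis section, which also names the key coefficient. The Aims place cognition and achievement after it. A reader might infer that the trial has no defined primary outcome at all; the documents do not support that. The domain is settled. What is unsettled is the rank of the other outcomes and which MVPA test decides.

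Alpha allocation and testing order are commonly left to an analysis plan, and none is shown. The 0.05 sentence could be read as a generic threshold that excludes no such procedure. This stands in part: the absence of a multiplicity procedure is not by itself a finding. But the label conflicts are in the text, and the analysis section goes beyond silence by drawing the conclusion from both model versions and setting one threshold for all analyses.

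Reporting unadjusted and adjusted estimates together is normal practice. A reader might infer that it doubles the number of tests; it does not in effect, as step 4 shows.

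The two programmes are distinct interventions, each tested separately, so pooling them into one family is debatable. That stands, and the 18.5% for one programme is then the relevant independent-test figure for MVPA.

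The lack of a power statement for cognition and academics is a weak point: a condensed article need not size every outcome. It serves here only as evidence of which outcomes the design treated as primary.

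**Conclusion.** The point holds as a contradiction in ranking combined with an open choice among MVPA tests. Cognitive and academic outcomes are primary in part of the abstract, in Table 1 and in a section heading, but secondary at the end of the abstract and outside the primary aim. Attendance is both primary and exploratory. Within MVPA, no measure, time contrast or model version is named as deciding.

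The ranking moves the nominal family from 8 to 28 tests, or 32 with attendance. Independence gives about 34% and 76% for the first two, and the assumed correlations about 26–30% and 48–71%. A reader might take 76% as the trial's false-positive rate. It is not: it is an upper guide that needs independent tests, the widest reading of the labels apart from attendance, and both programmes in one family. The label conflicts do not depend on any of these figures.

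**What to change.** **Labels.** Align the abstract, Table 1 and the section headings with the stated primary aim and the sample-size basis: MVPA primary, cognitive and academic outcomes secondary, attendance exploratory.

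**Deciding test.** State which MVPA measure, which time contrast and which model (unadjusted or adjusted) decide the primary conclusion, with the rest supportive. If both MVPA measures stay primary, as the Aims have it, state a multiplicity procedure across them. Whether to adjust jointly across the two programmes is the sponsor's choice. If school-time MVPA is chosen, note that its sizing used the percentage of recess time in MVPA, not minutes of school-time MVPA.

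**Timing.** Wave 2 post-intervention measurements were due in April–June 2017, after publication in October 2016, so this can precede the final data. By the article's dates the midpoint data and the Wave 1 post-intervention data were already due by publication, so the choice should be recorded as made without sight of results by arm.

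**Cost.** Naming one deciding test per programme costs only wording. Splitting the primary alpha in two lowers power for the school-time effect from about 81% to about 72% under the planned inputs. The actual enrolment restores about 81%, assuming 8 schools per arm and a single 25% loss; with 25% lost in each of two years it would be about 75%.

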**Discussion:**

The FLEX study will evaluate strategies for increasing children’s MVPA through two innovative, low-cost, school-based PA programs as well as their impact on children’s cognitive functioning and academic success. Demonstration of a relationship between school-based MVPA with neutral or improved, rather than diminished, academic outcomes in a naturalistic environment has the potential to positively influence investment in school PA programs and initiatives.

**Trial registration:**

ClinicalTrials.gov Identifier: NCT02810834. Registered May 11, 2015. (Retrospectively registered)

## Background

Physical activity (PA) plays a key role in childhood obesity prevention, in addition to conferring a number of other health benefits [1–4]. Yet fewer than half of all children in the U.S. meet the recommended 60 min of daily moderate-to-vigorous physical activity (MVPA) [5]. Schools are an ideal setting to achieve maximum impact with respect to improving PA levels, given the significant amount of time children spend in school over the course of their childhood [6]. Yet competing demands on teachers’ time, a crowded school curriculum, increased focus on standardized tests, and constrained school budgets have limited PA programming in schools [7, 8]. However, a growing body of evidence demonstrates that school-time PA is positively associated with academic achievement [9–13].

Novel strategies are needed to increase PA opportunities for children during school time. Recently, experts have called for a “whole school” approach to increasing children’s PA levels [14] in which recess, in-class PA breaks, before- and after-school programs, and integration of PA with academic curricula combine to create healthy school environments. Taken together, this comprehensive approach can increase time children spend engaging in MVPA to meet the recommendation of 60 min per day, 30 of which should be accrued during school hours.

Emerging evidence suggests that this “whole school” approach may be even more critical for underserved children. Compared to their higher-socio-economic status (SES) peers, children from low-income communities get a greater proportion of their total daily PA in school [15]. However, environmental barriers, such as limited PA-supporting policies, activities, and infrastructure, have been observed in lower-SES schools [16–18]. Under-resourced schools may face significant constraints to implementing school-based PA programs to supplement physical education (PE), thereby exacerbating disparities in PA, obesity, and academic achievement. Even short bouts of activity may predict determinants of future engagement in PA, suggesting that small increases in school-time MVPA could lead to additional increases in total daily MVPA and concomitant improvements in physical health and academic outcomes in underserved children [14, 19, 20].

Longitudinal evidence of the effects of school-based PA programs on physiological, behavioral, and academic outcomes is limited for racially diverse schoolchildren [14], and few studies have evaluated the impact of changes in MVPA on standardized test scores in this population in the context of a randomized school-based PA intervention study. The Fueling Learning through Exercise (FLEX) Study is a randomized controlled trial that seeks to evaluate the impact of two innovative school-based PA programs not only on MVPA, but also cognitive and academic outcomes over time among 3rd-5th grade children in underserved schools in northeastern United States. The primary aim of this paper is to describe the design and study protocol of the FLEX Study.

## Methods/Design

### Aims

The primary aim of the FLEX Study is to evaluate the impact of two school-based PA programs, *100 Mile Club®* and *Just Move™*, on children’s school-time MVPA and total daily MVPA, compared to a control group. In addition, the RCT will evaluate the effects of these innovative, school-based PA programs on children’s cognitive performance and academic achievement. The study will also evaluate the reach of the programs by examining factors that influence participation among different demographic, weight status, and fitness groups.

## Study design - overview

The FLEX Study is a cluster randomized controlled trial. Participating schools were clustered by location within the state and school district. Schools within each district were randomly assigned to receive a school-based PA intervention (*100 Mile Club* or *Just Move*) or assigned to be a control school. Third and fourth grade students were enrolled and are being followed for two school years (Fig. 1). Data are collected at three time points: baseline (fall, school year 1), short-term (spring, school year 1; 5–6 months post-baseline) and long-term post-intervention (spring, school year 2; ≈1.5 years post-baseline). The study occurred in two waves, the first beginning during the 2014–2015 school year (*n* = 6 schools) and the second wave during the 2015–2016 (*n* = 18 schools) school-year. Due to unforeseen weather circumstances and school cancellations in Winter 2015, additional student participant recruitment beyond the initial six schools was put on hold until the following school year. The investigative team determined that these schools would be designated as Wave 1. Approval for the study was obtained from the Tufts University IRB (Medford, MA) and additionally from individual school districts where required.

**Fig. 1 Fig1:**
[figure not shown]
Timeline for the FLEX study

## Setting & participants

### Schools

Identification of eligible schools began at the district level. The FLEX study is designed to examine health disparities among children associated with income and race/ethnicity. Therefore we targeted lower income and racially/ethnically diverse public school districts in Massachusetts. Initially, school districts were approached for participation if they had greater than 40 % of students qualifying for free or reduced price lunch and/or had greater than 40 % non-Caucasian students. In addition, districts were only approached if they had at least four elementary schools serving 3rd-5th graders.

Overall, twenty school districts were approached. Twelve of these districts declined to participate, citing changes in administration, ongoing participation in similar programs, and/or competing priorities. From the remaining eight districts, 24 schools agreed to participate and have at least one school enrolled. Six schools were included in Wave 1 and 18 schools in Wave 2. All districts serve a low-income and diverse population and are located in urban, suburban, and peri-urban areas. One exception to the initial inclusion criteria was made, such that one school from a district with 34 % low-income students was included.

### Students

All third and fourth grade students at participating schools were eligible to enroll. Third and fourth grade students were recruited in year one and followed in year two into fourth and fifth grade, respectively.

## Recruitment

### School recruitment & randomization

Schools were initially recruited by email and phone, followed with in-person meetings. Initial contact was made at the district level to superintendents and district wellness/health/PE coordinators, with secondary outreach at the individual school level (principals/assistant principals). Where districts have research boards/IRBs, contact was simultaneously made to those entities, and the study protocol and recruitment materials were submitted for approval. Once enrolled, schools were randomized to receive one of two school-based PA programs – *100 Mile Club* or *Just Move* – or to the control group. Schools were block randomized in groups of three, stratified by district, to ensure comparable numbers of schools in each arm. Once a school agreed to participate, the study statistician informed recruiting staff of the school’s group assignment. Throughout the school recruitment process, the statistician and recruitment staff worked independently. Figure 2 outlines the flow of district, school, and participant recruitment.

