### Student recruitment

Study staff conducted presentations in schools to explain the study and enrollment procedures, and to distribute recruitment materials to all 3rd and 4th grade students. Presentations were given assembly-style or in individual classrooms. Permission packets were sent home with each student and included: 1) a flyer with information about data collection procedures; 2) a plain language consent form for the parent/guardian; 3) a child assent form; and 4) a demographic form for the parent/guardian to complete. Permission packets were available in English, Spanish, Portuguese, Haitian Creole, Arabic, Vietnamese, and Mandarin, the primary languages spoken in targeted communities. Students were asked to return completed packets approximately 1 week after they were distributed. Enrollment was closed at the start of baseline data collection.

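### As written, recruiting staff learn a school's arm when the school agrees, apparently before children consent and baseline is measured, so who enrols can differ by arm

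*Protocol article*

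**What the plan says.** School recruitment & randomization sets the unit and timing of allocation: "Once enrolled, schools were randomized to receive one of two school-based PA programs" or control. It then gives the disclosure rule: "Once a school agreed to participate, the study statistician informed recruiting staff" of the arm. The one safeguard in that section is limited to the recruitment of schools: "Throughout the school recruitment process, the statistician and recruitment staff worked independently".

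Children enter afterwards and by another route. Under Students: "All third and fourth grade students at participating schools were eligible to enroll". The Student recruitment section describes how they were approached: "Study staff conducted presentations in schools to explain the study and enrollment procedures", with materials going to every child in the two grades. Packets with a parental consent form and a child assent form went home and were returned about a week later, and "Enrollment was closed at the start of baseline data collection".

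Under Sample size calculation and data analyses, the key term is the arm-by-time interaction on MVPA, with a random intercept for school. On adjustment: "We will examine both unadjusted and adjusted (including covariates such as sex, race/ethnicity, weight status) regression coefficients". The section does not say which of the two governs the conclusion.

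**The concern.** In a cluster trial, randomising schools makes the arms comparable in the children they contain. It makes them comparable in the children who enrol only if enrolment cannot depend on the arm. Here enrolment is voluntary, and the disclosure rule lets the people running recruitment, and possibly the school, know whether the school will get a running club, classroom activity breaks or a delayed programme. If active or motivated families volunteer more readily in one arm, the enrolled groups differ before treatment in ways that may predict how MVPA changes. A larger sample does not remove such a bias. It makes a false positive from a given bias more likely. Baseline measurements taken with the arm known could also be affected. The unadjusted comparison is the most exposed.

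**Working it through.** **1. Order of events**

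- A school agrees. This triggers both randomisation and disclosure to recruiting staff (School recruitment & randomization).
- Children are eligible only in participating schools (Students), so a school must have agreed before its children can be approached.
- Presentations, packets, consent and assent follow, and enrolment ends when baseline begins (Student recruitment).

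Disclosure is tied to agreement, and the approach to children requires agreement. Disclosure therefore comes first unless it was delayed, and no section mentions a delay. This is an inference; the text does not give the two dates. Table 1 and Process evaluation also schedule champion and teacher programme surveys at baseline in intervention schools. That fits the arm being known there by then, but does not date it against the children's consent.

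**2. The plan's own figures**

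- Inputs: 53.4 (SD 25.6) against 43.5 (SD 27.6), 80% power, significance at 0.05. Sidedness is not stated; two-sided reproduces the figure.
- Pooled SD = √[(25.6² + 27.6²)/2] = 26.6. Standardised effect = 9.9/26.6 = 0.37.
- Required size: 114 per arm by the normal formula; 114.5, so 115, by the t-based one. The plan states 115.
- Fixed clusters, 7 per arm, ICC 0.03: m = 115 × 0.97/(7 − 115 × 0.03) = 111.55/3.55 = 31.4, so 32 per school. Then 32/0.75 = 42.7, so 43, and 43 × 21 = 903, as stated.

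The design is thus meant to deliver the information of 115 independent children per arm.

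**3. What a bias would do to the error rate (assumed biases)**

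With bias b in SD units of the analysed outcome and no true effect, the test statistic is shifted by b/√(2/115) = b/0.132, and the error rate is Φ(−1.96 + shift) + Φ(−1.96 − shift).

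| Assumed bias (SD) | Shift | Two-sided error |
|---|---|---|
| 0 | 0 | 5.0% |
| 0.05 | 0.38 | 6.7% |
| 0.10 | 0.76 | 11.8% |

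A bias of 0.10 SD is 0.10/0.37 = 27% of the planning effect.

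**4. What could produce a bias of that size**

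The documents give neither consent rates nor eligible counts, so these are assumptions too. Suppose a child enrols when a normal willingness score exceeds a threshold, and the score has correlation ρ with the outcome. The mean shift among enrollers is ρ × φ(c)/p, where p is the consent rate and c its normal cut-off. The ratio φ(c)/p is 0.798 at p = 0.5, 0.966 at 0.4 and 1.159 at 0.3.

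| Consent rates in two arms | ρ = 0.1 | ρ = 0.3 |
|---|---|---|
| 40% and 50% | 0.02 SD | 0.05 SD |
| 30% and 50% | 0.04 SD | 0.11 SD |

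A bias near 0.10 SD therefore needs a 20-point consent gap together with the stronger correlation.

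**The case against.** The case against has real force on size.

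- **The order is inferred.** The disclosure rule speaks of recruiting staff and the student section of study staff. The text does not say that they are the same people, or that families were told the arm. This lowers certainty, but nothing in the text separates the two groups or describes blinding.
- **Staff do not select children.** All third and fourth graders were approached, the flyer describes data collection, and no section makes study consent a condition of taking part in a programme. Control schools also get a programme later. Any bias must therefore act through differential consent, which is a weaker route but still open.
- **The outcome is change from baseline.** Stable differences, such as more active children enrolling in one arm, drop out. Selection linked to trend or to response does not, and protection from it no longer comes from randomisation.
- **Remedies are partly planned.** Adjusted models are specified, and Academic outcomes already plans school-level analysis of grade-level scores. Naming the main model is often left to an analysis plan. The disclosure rule itself, however, is stated here and is the weak point.

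A reader might infer that enrolment did differ by arm, because it averaged 174/6 = 29 per school in Wave 1 and 1008/18 = 56 in Wave 2. The documents do not support that: the contrast is between waves, randomisation was in blocks of three within district, and Wave 1 met severe weather. A reader might also put the bias at 0.2 SD, which would give about 33% error. The arithmetic is right, but no source supports that size and it lies outside the scenarios above.

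**Conclusion.** The point holds as a design weakness. The rule allows children's consent and baseline measurement to take place with the arm known, and the stated safeguard stops at the recruitment of schools. An imbalance is neither shown nor excluded, because the text has no enrolment counts by arm and Figure 2, which may hold them, is not shown.

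The size is illustrative: about 7% to 12% error for an assumed bias of 0.05 to 0.10 SD, and close to 5% if the bias is about 0.02 SD. These figures rest on an effective 115 children per arm and on a bias expressed in SDs of the analysed outcome. The 0.37 SD yardstick comes from a between-group comparison of the share of recess time spent in MVPA, and the document gives no SD for change in MVPA minutes that could replace it.

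**What to change.** **The rule.** In School recruitment & randomization, have the statistician release a school's assignment to recruiting staff and to the school only after student enrolment has closed and baseline is complete at that school. Use the same arm-neutral presentation in every school. The cost is a change of wording and a short delay to champion and teacher training.

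**Schools whose assignments are already released.** Baseline ended by February 2016 in both waves (Data collection methods), before the article appeared, so in this trial the later release cannot help and these steps are the usable ones:

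1. In Sample size calculation and data analyses, name the analysis adjusted for pre-treatment child covariates as the main one: sex, grade, race/ethnicity, lunch eligibility and baseline BMI z-score. Make the unadjusted analysis supportive. The data come from the baseline collection. Adjustment deals only with measured factors.
2. Report enrolled over eligible children by school and arm. This needs third- and fourth-grade roll counts. It shows whether uptake differed but corrects nothing.
3. Use the grade-level test scores already planned under Academic outcomes as a check on the academic result that does not depend on study consent. It says nothing about MVPA.

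Wave 2 post-intervention measurement was set for April to June 2017, after publication, so the choice of main analysis could still be fixed before those data existed.
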